## 7.2 Study assessments

Key outcomes will be assessed at baseline and at the end of the intervention. Drawing of blood (IL-6) and neurological investigations (EEG and CPM) will be undertaken. Pain outcomes will be based on daily numeric rating scale (NRS) for non-cyclical pelvic pain and a separate NRS for menstrual pain. The Clinical Global Improvement (CGI) scale and The Endometriosis Health Profile (EHP-30) [36] will be used as secondary quality of life outcomes. Financial and personal impact of endometriosis will be collected via the ENDOCOST questionnaire [37]. Data will also be collected on safety and expectation (using the EXPECT questionnaire).Daily data on rescue medication use, presence and severity of other endometriosis symptoms (dyspareunia, dyschizia, dysuria) will be collected on the daily pain diary. Feasibility outcomes will include an assessment of interest to participate in the trial, identification of appropriate recruitment strategies, the appropriateness of eligibility criteria, compliance with treatment attendance and data collection, and dropout rates.

# 8. Data Collection

Baseline demographic data on age, ethnicity, menstrual history, smoking, current medication and revised American Society of Reproductive Medicine (rASRM) classification [38] of endometriosis will be collected by the primary investigator ([name]) at prior to the first acupuncture session. Baseline pain scores for both non-cyclical and menstrual pain will be collected prior to trial entry. The EXPECT questionnaire will be used to determine expectancy and belief in acupuncture.

*Primary outcome measure:*

The primary outcome measures are daily 0-10 numeric rating scale (NRS) for non-cyclical pelvic pain and a separate daily 0-10 NRS used for menstrual pain during the period itself.

*Secondary outcome measures:*

The Clinical Global Improvement (CGI) scale and The Endometriosis Health Profile (EHP-30) [36] will be used as secondary quality of life outcomes. Data will also be collected on safety, expectation, rescue medication use, presence and severity of other endometriosis symptoms (dyspareunia, dyschizia, dysuria) as well as the financial and personal impact (e.g time off work, additional help required at home) of endometriosis related symptoms. Feasibility outcomes will include an assessment of interest to participate in the trial, identification of appropriate recruitment strategies, the appropriateness of eligibility criteria, compliance with treatment attendance and data collection, and dropout rates. components of the consultation and treatment sessions were important.

*Quality assurance:*

Quality assurance measures on needling technique will be carried out on practitioners during the study period by using an independent acupuncturist to check point selection and location at least once for each practitioner.

*Biomarkers:*

Drawing of blood (IL-6) will be undertaken by PI [name] at baseline and at completion and neurological investigations (EEG and CPM) will be undertaken at baseline and again at the conclusion of treatment by PI [name] and PI [name].

Human electroencephalography (EEG) is a non-invasive recording technique that captures ongoing electrical brain activity via strategically placed scalp electrodes. The excellent temporal resolution of EEG makes it the ideal methodological approach for investigating the neural mechanisms associated with intervention-related changes. Participants will have an electrode cap fitted and resting-state EEG activity recorded for 10 minutes. A simple auditory discrimination task will then be presented to assess whether the intervention has affected the activated brain state.

Conditioned pain modulation (CPM): CPM is a well-established, reliable and safe measure of pain processing that is thought to indicate the function of descending pain control systems. This is examined as a change in the pain perceived in one body region (test stimulation) as a result of pain induced in another body region (conditioned stimulation). We will use PPT measurement as the test stimulation and heat pain (1°C above HPT) or cold pain (3°C ice bath) as the conditioned stimulation using the CPM System (Thermal Sensory Analyzer, TSA-2001, Q-Sense-CPM, Medoc Ltd, Ramat Yishai, Israel). Three PPTs (test stimulation) will be measured before the application of heat or cold pain (conditioned stimulation). Either heat or cold pain will be used. The heat pain will be applied via a 30 x 30 mm thermode on the volar surface of the forearm. Cold pain will be applied via placing the subjects dominant hand (to the wrist) in a circulating water bath at a cold temperature (maximum 3 °C) for 2 minutes. The water temperature will be checked prior to each test to ensure that it was in accordance with the protocol. Three PPT measurements will be repeated 30 seconds after applying the conditioned stimulation. Participants will be asked to rate their pain during conditioned stimulation on a numeric rating scale (0-100) at 0 s, 30 s and at the end of the trial. Pain scores will be maintained between 50 and 80/100 during testing.

# 9. Statistics and Data Analysis

## 9.1 Sample Size calculation:

There is no sample size calculation undertaken for this study due to its nature as a feasibility study. A previous feasibility study on acupuncture [39] has shown that a sample size of 30 is sufficient to provide data on feasibility outcomes.

## 9.2 Proposed Analysis:

Baseline demographics will be reported using descriptive statistics along with recruitment rates and other feasibility data. NRS levels for pain and CPM will be analysed using a mixed model ANCOVA. Changes in IL-6 levels will be assessed using a paired t-test. Categorical data such as expectation will be analysed using Fishers exact.

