# 2. Study Objectives

The aim of this study is to (1) assess the feasibility and acceptability of acupuncture and (2) to investigate any changes in neurological or biomarkers when using acupuncture to treat endometriosis-related chronic pelvic pain.

The specific objectives are (1) To determine barriers to recruitment, appropriateness of eligibility criteria, acceptability and adherence to treatment in women with endometriosis related CPP. (2) To determine the minimal clinically important reduction in pain from endometriosis (3) To determine which, if any, objective markers of endometriosis CPP are altered by acupuncture (4) To determine if the endogenous pain modulation system is affected in women with CPP.

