# 3. Study Design

A randomised controlled feasibility trial comparing acupuncture plus usual care to usual care alone for women with endometriosis related CPP.

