# 4. Study Population

## 4.1 Sample Size

30 women in total, 15 participants per group.

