5.5.2 Treatment allocation

Randomization will be 1:1 into one of two study groups:

Manual acupuncture + usual care:

Women in this group will receive 16 acupuncture treatments over 8 weeks (twice weekly – with a minimum of 2 days between treatments) in addition to their usual care, delivered by registered Chinese medicine practitioners in private clinics or at the clinic room (5.LG.07) at the National Institute for Complementary Medicine. Manual acupuncture will be delivered using a semi-standardized protocol based on previous research [14, 33].

Usual care:

Participants will continue with the usual care as currently prescribed or advised by either their general practitioner or gynecological specialist. Usual care will be based on specific medical advice that has been given to the participant, but commonly involves the oral contraceptive pill or non steroidal anti inflammatories or analgesic medication.

5.5.3: Withdrawal procedures

If a participant wishes to withdraw from the trial they will be immediately removed from treatment.

If a participant withdraws during intervention they will not be replaced however if they withdraw post randomization but prior to the first treatment they will be replaced.

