## 6.2 Control group

Participants will continue with the usual care as currently prescribed or advised by either their general practitioner or gynecological specialist. The use of usual care alone will allow the natural progression and fluctuations in CPP to be isolated from the effect of acupuncture.

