Participants will undergo a conditioned pain modulation test to measure the function of their descending pain systems. This test involves applying pressure stimuli to one part of the body while another part of the body is experiencing heat or cold pain. In this study we will be applying stimuli to the volar surface of the forearm. There are no risks associated with pressure stimuli. Some discomfort may be present when the pressure sensation first changes to one of pain. However, as this is a threshold test, the pressure stimulus will be ceased as soon as the participant notes that the sensation has changed from pressure to pain. There is a small risk of a burn with any application of heat. The risk of a burn will be reduced by screening and excluding participants with reduced peripheral sensation. In the unlikely event of a burn, standard operating procedure for treatment of a burn will be implemented. All staff will be familiar with these procedures.

The EEG, conditioned pain modulation and blood samples will all be taken during a single session at the same location at the National Institute of Complementary Medicine prior to receiving any trial intervention. This will be repeated at the conclusion of the trial intervention, or after 8 weeks in women who are allocated to usual care.

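### The only IL-6 analysis named is a paired t-test, which compares women with themselves and cannot show whether acupuncture altered IL-6

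*Protocol*

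**What the plan says.** Section 9.2 of the protocol gives IL-6 one analysis: "Changes in IL-6 levels will be assessed using a paired t-test". It does not say in which women the test is run, and it names no other IL-6 analysis. The sentence before it treats the other outcomes differently: "NRS levels for pain and CPM will be analysed using a mixed model ANCOVA".

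The objective that IL-6 serves is the third in section 2: "To determine which, if any, objective markers of endometriosis CPP are altered by acupuncture". Section 3 describes the design as "A randomised controlled feasibility trial comparing acupuncture plus usual care to usual care alone for women with endometriosis related CPP", section 5.5.2 sets allocation at 1:1, and section 4.1 gives the size: "30 women in total, 15 participants per group". Section 6.2 explains why there is a control arm: "The use of usual care alone will allow the natural progression and fluctuations in CPP to be isolated from the effect of acupuncture". Section 7.1 has blood taken before any intervention and again at the end of treatment, or after 8 weeks in the usual-care arm.

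**The concern.** Whether a marker is altered by acupuncture is a causal question. In this design it is answered by comparing the randomised arms. A paired t-test asks something else: whether mean IL-6 moved between two time points. Anything that moves IL-6 in both arms enters that test together with any effect of acupuncture.

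The protocol gives reasons to expect some shared movement. Women must score at least 4/10 on a symptom to enter (section 4.3), so some regression toward the mean is likely. Section 1.1 says IL-6 changes with symptom severity during treatment. Analgesics are allowed as needed in both arms (section 6.3.1).

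At stake is the reading of one of the candidate markers for the full trial that section 1.2 anticipates. A false IL-6 signal could lead to the wrong marker being carried forward. A real effect could also be hidden if usual care drifted the other way. The data for the right comparison are collected, but the named test does not use them for it.

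**Working it through.** **Nothing to reproduce.** The protocol states no alpha, effect size, SD, correlation or expected change for IL-6. The argument in step 1 needs no numbers. The rates in steps 2 to 4 are illustrations under stated assumptions.

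**Step 1: what each version of the test estimates.** Let δ be the mean IL-6 change that both arms share and τ the effect of acupuncture, with 15 women per arm (section 4.1).

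- Acupuncture arm only: mean change = δ + τ.
- Usual-care arm only: mean change = δ.
- All 30 pooled: (15(δ + τ) + 15δ)/30 = δ + τ/2.
- Difference between arms: (δ + τ) − δ = τ.

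Only the last isolates τ, and no paired t-test computes it. Separate tests in each arm do not fill the gap, because significance in one arm and not in the other is not a test of the difference.

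**Step 2: how often the paired test rejects when τ = 0.** Assumptions: two-sided alpha 0.05, normal data, shared change d in units of the SD of the change scores. The rejection probability p comes from the noncentral t distribution with n − 1 degrees of freedom and noncentrality d√n. For d = 0.5 and n = 15 the noncentrality is 0.5 × √15 = 1.94, and p = 0.438. With independent arms and the same p in each, the probability of significance in acupuncture but not usual care is p(1 − p), and in exactly one arm 2p(1 − p). At d = 0.5 these are 0.438 × 0.562 = 0.246 and 0.492.

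| Shared change d | Acupuncture arm, n = 15 | Pooled, n = 30 | Acupuncture only, p(1 − p) | Exactly one arm, 2p(1 − p) |
|---|---|---|---|---|
| 0 | 5.0% | 5.0% | 4.8% | 9.5% |
| 0.25 | 14.7% | 26.3% | 12.6% | 25.1% |
| 0.5 | 43.8% | 75.4% | 24.6% | 49.2% |
| 0.75 | 77.1% | 97.8% | 17.7% | 35.3% |
| 1.0 | 94.9% | about 100% | 4.8% | 9.7% |

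At d = 0.3 and 0.8 the acupuncture-arm test rejects in 19.2% and 82.1% of trials. Significance in acupuncture only then occurs in 0.192 × 0.808 = 15.5% and 0.821 × 0.179 = 14.7%.

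**Step 3: the same with drift in baseline SDs.** If baseline and follow-up have equal SDs and correlate at r = 0.6 (assumed), the SD of change is √(2 − 2 × 0.6) = 0.894 baseline SDs. Drifts of 0.3 and 0.5 baseline SD are then d = 0.335 and 0.559, and the acupuncture-arm test rejects in 22.8% and 52.2% of trials. A simulation of 4,000 trials gave 22.9% and 52.4%, and 4.2% at zero drift. These rates count the acupuncture-arm test alone.

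**Step 4: what a between-arm analysis does on such data.** Ten thousand simulated trials of 15 + 15 women, r = 0.5, τ = 0:

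| d | Paired test, acupuncture arm | t-test of change between arms | ANCOVA on baseline and arm |
|---|---|---|---|
| 0 | 4.6% | 4.6% | 4.6% |
| 0.5 | 43.9% | 5.1% | 5.2% |
| 1.0 | 95.0% | 5.0% | 5.1% |

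In the r = 0.6 simulation ANCOVA rejected in 4.5%, 4.8% and 5.1% of trials at drifts of 0, 0.3 and 0.5 baseline SD. The between-arm analyses hold their level whatever the shared change.

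**The case against.** The best case for leaving the sentence alone is proportion. This is a feasibility study of 30 women with no sample size calculation. Section 8 lists IL-6 under biomarkers, apart from the primary and secondary outcomes, and no sample size, stopping or progression decision depends on it. The second aim in section 2 speaks of investigating changes when acupuncture is used, which a within-woman analysis partly serves. Both arms are sampled twice, so a between-arm analysis remains possible, and an unseen SAP may contain one.

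This limits the consequences but does not remove the fault. A feasibility label excuses imprecision; it does not excuse a test that cannot address a stated objective. The protocol names this test and no other for IL-6, so this is more than detail left to a SAP.

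Three further points do stand:

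- Section 9.2 does not say where the test is run. If it is run in each arm and shown side by side, a change significant in both arms would be seen as shared, so misattribution would be partial. On that reading the acupuncture-only column applies, not the higher rates.
- The size of any shared change is unknown. Unsynchronised cycle phase would mainly add noise rather than shift the mean. At zero drift the paired test rejects no more often than ANCOVA.
- A log scale and a ratio estimate are reasonable for a cytokine but rest on no distribution given in the protocol. They are optional; the between-arm contrast is not.

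**Conclusion.** The point holds. The one analysis the protocol names for IL-6 does not match Objective 3 and makes no use of randomisation, although the data for a randomised comparison are collected. IL-6 is the only marker whose named analysis is purely before-after; pain and CPM have an ANCOVA, and no EEG analysis is named.

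With no acupuncture effect and a shared change of 0.3 to 0.8 SD of change, the acupuncture-arm test would be falsely significant in 19.2% to 82.1% of trials. Significance in acupuncture only would occur in about 15% to 25%. A between-arm ANCOVA stays at about 5%. These rates depend on 15 women per arm, alpha 0.05, normal data and an assumed drift, and they are not predictions for this trial. The conclusion does not depend on them: even with no drift, the paired test estimates no difference between arms.

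**What to change.** Replace the IL-6 sentence in section 9.2 with wording such as: IL-6 at completion will be compared between the randomised arms by ANCOVA with baseline IL-6 as covariate, women being analysed in the arm to which they were randomised, and the adjusted difference will be reported with a 95% CI; changes within each arm will be described only. If a log scale is chosen, the result becomes a ratio with its 95% CI.

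The protocol or SAP should also say how women without a completion sample, and those replaced under section 5.5.3, are handled.

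The cost is a one-sentence change to the analysis section, plus that clarification. No extra blood samples, visits or patients are needed.

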There is little high quality evidence for using acupuncture in the treatment of endometriosis [13] however two recent studies have shown significant promise in reducing endometriosis related CPP using a short course (10-16 treatments) of acupuncture. One trial [14] found clinically significant reductions in VAS pain scores (-5.4 vs -1.2) and one trial [15] a reduction in a numerical rating scale (NRS) for pain (MD -1.4, 95% CI -2.6 to -0.2). Both trials compared acupuncture to different styles of sham acupuncture. However both trials suffer a number of methodological issues such as very small sample sizes [15], less common Japanese style of acupuncture [15] or the use of a cross-over design [14] which may not be appropriate in trials of acupuncture for cyclical pain issues. Acupuncture has multiple mechanisms by which it may reduce endometriosis related CPP including the potential to reduce PGE2 expression [16] reduce NGF [17], increase endogenous opioid release [18] and reduce mechanical allodynia [17].

*Neurological and biomarkers in Endometriosis related Chronic Pelvic Pain:*

Using neurological or biomarkers in conjunction with clinical outcomes has the potential to fill a significant gap in our current knowledge on acupuncture’s potential mechanism(s) of action and is a key area for acupuncture research according to a recent whitepaper written by the Society for Acupuncture Research (SAR) [19]. Interleukin-6 (IL-6) is a cytokine and inflammatory marker implicated in the pathogenesis of endometriosis[8]. Serum IL-6 levels are raised in women with endometriosis [20, 21], and, are positively correlated with disease stage [22] and change in response to symptom severity during treatment [23]. Acupuncture has been shown to reduce IL-6 levels [16, 17]. To date there has been one small study that has examined the effect of Japanese acupuncture vs sham acupuncture on IL-6 in women with endometriosis but due to severe recruitment issues the study was underpowered to detect any differences between groups [24]. Therefore acupuncture’s effect on IL-6 in endometriosis remains unclear.

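### IL-6 is to be tested by a paired t-test on changes in level with no transformation named; a baseline-adjusted between-arm comparison of log IL-6 would be a better choice at little cost

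*Protocol*

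**What the plan says.** The whole IL-6 analysis is one sentence in Protocol 9.2: "Changes in IL-6 levels will be assessed using a paired t-test". It names no scale, transformation or between-arm comparison. The same section plans a mixed model ANCOVA for the pain ratings and for CPM, but not for IL-6.

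The setting is as follows.

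- **Design (Section 3):** "A randomised controlled feasibility trial comparing acupuncture plus usual care to usual care alone for women with endometriosis related CPP".
- **Size (Section 4.1):** "30 women in total, 15 participants per group".
- **Sampling (Section 8):** blood is drawn twice from each woman, at baseline and at completion.
- **Purpose (Section 2, third objective):** "To determine which, if any, objective markers of endometriosis CPP are altered by acupuncture".
- **Power (Section 9.1):** "There is no sample size calculation undertaken for this study due to its nature as a feasibility study".

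Section 1.1 introduces IL-6 as a cytokine and inflammatory marker. Nowhere does the protocol describe its distribution, variability or expected change.

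**The concern.** A t-test on change in level weights every unit of concentration equally. If IL-6 is a positive, right-skewed measurement and acupuncture lowers it by a percentage, women who start high contribute much larger absolute changes than women who start low. With 15 women, the mean and SD of change then depend largely on one or two of them. On the log scale a given percentage fall counts the same in every woman.

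IL-6 is the only blood marker and serves the third objective. Section 1.2 says the data on these markers are only preliminary and need to be understood before a full trial. An inefficient scale makes a real change harder to see, and it hands the next trial an effect estimate and SD that are hard to use.

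The same sentence also leaves the usual-care arm out of the test. That matters for the remedy, because taking logs alone would not turn a before-after test into an answer to the third objective.

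**Working it through.** The plan gives no IL-6 power, SD or effect, so there is no figure to reproduce.

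**Inputs from the protocol:** 15 per arm (4.1), 1:1 allocation (5.5.2), one baseline and one completion value per woman (8), paired t-test on change (9.2).

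**Assumed inputs:** two-sided 5% level; no dropout; IL-6 lognormal with log-SD 0.3 to 1.0; correlation 0.5 to 0.7 on the log scale; a proportional fall of 30% or 40% in the acupuncture arm and none under usual care.

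**Check of one log-scale case by formula** (log-SD 0.8, correlation 0.7, 40% fall):

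- Effect: ln(0.6) = −0.511.
- Paired test: SD of log change = 0.8 × √(2 × (1 − 0.7)) = 0.620. Noncentrality = 0.511 × √15 / 0.620 = 3.19 on 14 degrees of freedom, which gives power of about 84%.
- ANCOVA: residual SD = 0.8 × √(1 − 0.7²) = 0.571. Standard error = 0.571 × √(2/15) = 0.209. Noncentrality = 0.511 / 0.209 = 2.45 on 30 − 3 = 27 degrees of freedom, before a small loss from chance baseline imbalance.

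**Simulation:** 20,000 trials per setting (standard error of each power at most 0.35 points). The paired test is in the acupuncture arm. Power in %, raw → log:

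| Fall, correlation | Log-SD | Paired t-test | Between-arm ANCOVA |
|---|---|---|---|
| 40%, 0.7 | 0.3 | 100 → 100 | 100 → 100 |
| 40%, 0.7 | 0.5 | 98.7 → 99.7 | 92.3 → 96.0 |
| 40%, 0.7 | 0.8 | 65.2 → 84.1 | 47.6 → 63.5 |
| 40%, 0.7 | 1.0 | 39.4 → 66.6 | 28.1 → 46.5 |
| 30%, 0.5 | 0.3 | 98.4 → 99.0 | 93.1 → 94.3 |
| 30%, 0.5 | 0.5 | 65.4 → 72.6 | 51.1 → 57.4 |
| 30%, 0.5 | 0.8 | 25.7 → 36.7 | 20.1 → 26.8 |
| 30%, 0.5 | 1.0 | 14.3 → 25.2 | 12.0 → 18.4 |

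The largest gains are 66.6 − 39.4 = 27.2 points (paired) and 46.5 − 28.1 = 18.4 points (ANCOVA). The smallest are zero, where power is already at its ceiling.

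**Dominance by a few women** (40% fall, correlation 0.7): the two largest raw changes in the acupuncture arm typically supply about 53% of the sum of squared changes at log-SD 0.5, 67% at 0.8 and 73% at 1.0.

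**Type I error** with no change in either arm: about 3 to 5% on the raw scale and about 5% on the log scale.

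**Contrary case.** Take IL-6 as roughly normal with mean 3, SD 1 and an additive fall (again assumed). With correlation 0.5 and a fall of 1, ANCOVA power goes from 85.2% raw to 75.1% log, a loss of 10.1 points. With correlation 0.7 and a fall of 0.5, paired power goes from 64.5% to 53.5%, a loss of 11.0 points.

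**Why logs alone are not enough.** Suppose both arms fall by 20% for reasons unrelated to acupuncture (log-SD 0.5, correlation 0.7). The paired test on log values is then significant in the acupuncture arm in 54% of trials. The two arms are independent, so it is significant there and not under usual care in about 0.54 × (1 − 0.54) = 25%.

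**The case against.** The strongest reply is that 9.2 names a test and not a scale. A paired t-test on log values is still a paired t-test, and transformation, assay-limit rules and rank-based checks commonly wait for an SAP, which is not shown here. This stands in part: the protocol never says the values are untransformed. But a change in levels tested by a t-test reads most naturally as a difference in concentration, so the sentence makes a choice that an SAP would normally carry out.

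Second, lognormal data with a proportional effect favour the log scale by construction. That is correct. The gain is conditional, and the near-normal case shows it can reverse.

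Third, this is a feasibility study with no power target, and no primary outcome rests on IL-6. That also stands and limits the importance of the point.

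A reader might go further and infer that the plan forfeits a definite amount of between-arm power, recoverable for nothing. The documents do not support that. No between-arm IL-6 test is planned, so there is no planned between-arm power to lose. No figure for IL-6 variability or effect is given, so no single number belongs to this plan. The change also has costs, though small ones. Nor should a reader infer that raw-scale testing produces false positives through skewness: under lognormal data it is, if anything, slightly conservative.

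**Conclusion.** The point holds in conditional form. As naturally read, 9.2 tests arithmetic change in IL-6 in small arms. If IL-6 is right-skewed and changes proportionally, this costs about 0 to 27 points of power in the planned paired test over the assumed range, and about 0 to 18 points if a between-arm ANCOVA were run on the raw rather than the log scale. If IL-6 is near normal with an additive effect, logs lose about 10 points. Validity in the type I error sense is not harmed by the scale.

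These gains compare the same test on two scales. Moving from the paired test to ANCOVA does not by itself raise power: at log-SD 0.8, correlation 0.7 and a 40% fall, the planned raw paired test has 65% and the log ANCOVA 64%. The reason to move is that only the second compares the randomised arms, which the third objective needs.

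Importance is modest.

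**What to change.** In 9.2, replace the IL-6 sentence with a between-arm ANCOVA:

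log(IL-6 at completion) = a + b × log(baseline IL-6) + c × arm.

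Report exp(c), the ratio of geometric means for acupuncture plus usual care against usual care alone, with a 95% interval. State in advance a fixed rule for values below the assay limit, and show a rank-based between-arm analysis as a check. This also brings IL-6 into line with the ANCOVA already planned for pain and CPM.

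The cost is a sentence or two, with no extra women or blood samples. Results are read as percentage rather than concentration change, the assay-limit rule has to be settled before the data are seen, and some power may be lost if IL-6 proves not to be skewed.

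### The only rule for categorical data, Fisher's exact test, ignores order if graded answers keep three or more levels; a rank or ordinal method would use it

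*Protocol*

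**What the plan says.** Section 9.2 assigns a mixed model ANCOVA to the pain scores and conditioned pain modulation, and a paired t-test to IL-6. For everything categorical it says "Categorical data such as expectation will be analysed using Fishers exact". Expectation is the only variable named under that rule.

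Section 8 describes the expectation measure alongside the baseline data: "The EXPECT questionnaire will be used to determine expectancy and belief in acupuncture". It also lists expectation among the secondary outcomes. On global improvement it says "The Clinical Global Improvement (CGI) scale and The Endometriosis Health Profile (EHP-30) [36] will be used as secondary quality of life outcomes". The protocol names no test for the CGI, and it gives neither the number of response levels nor the response format for the CGI or EXPECT.

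On size, section 4.1 has "30 women in total, 15 participants per group" and section 5.5.2 has "Randomization will be 1:1 into one of two study groups". Section 9.1 states that "There is no sample size calculation undertaken for this study due to its nature as a feasibility study". No alpha, effect size or power target is given for any categorical outcome.

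**The concern.** The rule covers a class of data and gives an example, so it is a stated choice of method and not a detail left open. Degree of expectation and degree of improvement are graded by nature. Fisher's exact test on a table with more than two categories gives the same p-value however the categories are arranged. It therefore cannot tell a steady shift towards better answers from a scattered difference of the same probability.

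With 15 women per arm, a secondary improvement scale kept in graded form could be read with a test that discards part of its information. Expectation raises a separate matter. If it is measured before randomisation, any difference between the arms is due to chance, and a between-arm test answers no useful question.

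**Working it through.** The protocol gives no power figure to reproduce, so the check asks what ignoring order would cost at this trial's size.

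**Inputs from the protocol.** 15 and 15 women (sections 4.1 and 5.5.2); Fisher's exact test (section 9.2).

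**Assumed inputs, none of them in the protocol.** Two-sided 5% level; no dropout; 3, 5 or 7 levels; equal or peaked control distribution; a proportional-odds shift with odds ratio (OR) 2 to 12.

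**Shift.** If c is the control arm's cumulative probability up to a level, the other arm has odds c/(1 − c) divided by OR. Example with 5 equal levels and OR 4: control cumulative values 0.2, 0.4, 0.6, 0.8 have odds 0.25, 0.667, 1.5, 4. Divided by 4 these are 0.0625, 0.167, 0.375, 1, which give cumulative values 0.059, 0.143, 0.273, 0.5. The level probabilities are then 0.059, 0.084, 0.130, 0.227, 0.500, against 0.2 each in the control arm.

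**Fisher (Fisher-Freeman-Halton).** With t_j women at level j, a_j of them in one arm, a table has probability ∏C(t_j, a_j) / C(30, 15). The p-value sums this over all tables with the same margins that are no more probable than the one observed. The product does not change when levels are reordered, which is the point at issue.

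**Wilcoxon.** W = Σ a_j m_j, where m_j are midranks, with mean 15 × 31 / 2 = 232.5 and variance (15 × 15 / 12) × [31 − Σ(t_j³ − t_j) / (30 × 29)]. The main grid uses the normal approximation with a 0.5 continuity correction.

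Each cell has 1,500 simulated trials, so the Monte Carlo standard error is at most √(0.5 × 0.5 / 1,500) = 1.3 points.

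Power in %, Fisher → Wilcoxon, with the gain taken from unrounded values:

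| Levels | OR 2 | OR 3 | OR 4 | OR 6 | OR 8 | OR 12 |
|---|---|---|---|---|---|---|
| 3 equal | 12 → 16 (+4) | 25 → 34 (+9) | 37 → 49 (+12) | 52 → 65 (+13) | 63 → 76 (+13) | 80 → 88 (+8) |
| 5 equal | 10 → 16 (+6) | 21 → 35 (+15) | 33 → 53 (+20) | 51 → 73 (+22) | 65 → 84 (+19) | 81 → 94 (+13) |
| 5 peaked | 11 → 17 (+6) | 18 → 34 (+16) | 29 → 52 (+22) | 50 → 72 (+22) | 64 → 86 (+22) | 81 → 94 (+14) |
| 7 equal | 9 → 17 (+8) | 19 → 39 (+20) | 28 → 54 (+26) | 45 → 73 (+28) | 63 → 85 (+22) | 79 → 94 (+15) |
| 7 peaked | 9 → 16 (+8) | 15 → 33 (+18) | 24 → 50 (+25) | 42 → 72 (+31) | 57 → 84 (+27) | 74 → 93 (+19) |

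**Cross-checks.**
- Separate runs with permutation p-values at OR 4, 6 and 9 gave gains of 28, 33 and 27 points with 7 levels (24 → 52, 42 → 75, 63 → 90) and 20, 22 and 19 points with 5 levels (31 → 51, 50 → 72, 69 → 88). The 33 is close to the grid's maximum of 31, given simulation error and a possibly different distribution.
- A further run with 3 levels at OR 2 gave 12 → 15, a gain of 3 points.
- The grid was rerun with exact Wilcoxon p-values, because the normal approximation flatters the rank test when levels are few. With 5 or 7 levels the picture was the same. With 3 levels the gain was about 3 to 9 points, so the upper part of the 3 to 13 range comes from the approximation. With two categories the exact rank test and Fisher's exact test agreed, so nothing is lost.

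**Where the order reverses.** With 5 levels and arms differing in spread only (control 0.05, 0.2, 0.5, 0.2, 0.05; other arm 0.35, 0.1, 0.1, 0.1, 0.35), Fisher has 86% power and Wilcoxon 7%.

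**The case against.** Fisher's exact test is valid here: its size is controlled. The trial is a feasibility study that makes no power claim, and a statistical analysis plan not shown here may settle the handling of each scale. All of this stands, and it limits the weight of the point.

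Four stronger readings are tempting and should be resisted.

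- *That the protocol assigns Fisher's exact test to the CGI.* It does not. Section 9.2 names only expectation. The inference is reasonable, since no other method in 9.2 is directed at such a scale, but it remains an inference. If the CGI is reduced to improved or not improved, Fisher's exact test is a sound choice.
- *That the trial loses a fixed 20 points of power or more.* Losses of that size arose only on the longer scales with large shifts. Every input to them apart from the arm size is assumed.
- *That the test of expectation is a test of a hypothesis true by design.* This holds only if expectation is measured before randomisation and compared between arms. Section 5.3 places randomisation after baseline data, but section 8 both describes EXPECT beside the baseline data and lists expectation as a secondary outcome, and section 7.2 gives it no time point. Participants are told their allocation (section 5.5.1), so later expectation could truly differ. Section 9.2 does not say which comparison is meant.
- *That the value of expectation as a predictor is left unused.* The protocol does not settle this either way.

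What the objection does not remove is that a rule written for all categorical data is poorly suited to ordered answers, and that the better method is easy to name.

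**Conclusion.** The point holds in conditional form. For outcomes kept as three or more ordered levels and differing by a consistent shift, the stated rule gives away power at 15 per arm. The loss ranges from a few points (three levels, or a modest shift) to about 30 points (seven levels, OR near 6). It shrinks again at very large shifts, where both tests approach full power. These figures rest on proportional odds, complete data and a two-sided 5% level.

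For expectation measured before randomisation, power is not the issue; a between-arm test is simply not needed. Since no power is claimed and these are secondary or descriptive comparisons, this is a desirable improvement and not a flaw that threatens the trial.

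**What to change.** In section 9.2, replace the sentence on categorical data with wording to this effect: *Binary or unordered categorical data will be compared with Fisher's exact test. Ordered outcomes measured after randomisation, such as the CGI if kept graded, will be compared with an exact Wilcoxon-Mann-Whitney test or a proportional odds model, with an effect estimate and confidence interval. Expectation, where measured before randomisation, will be described by arm without a between-arm test.*

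The same edit should state when expectation is measured and whether the CGI is analysed in graded or two-category form.

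The cost is a few lines of text and no new data. The one statistical downside is that a rank test has little power against a difference in spread alone, which is not the question of interest for an improvement scale.
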